### Data collection and management

The data collection schedule is illustrated in Fig. 2. Data will be obtained from the Ochiai Hospital. The investigator will collect the potential participants’ information (name, home address, date of birth, and contact number) during the first visit to the hospital after recruitment. The participants will be assigned a participant identification code after trial enrolment and their data will be managed according to it. A list of the participants’ personal information, participant identification codes, consent forms, case report forms, and other documents or records necessary to ensure data reliability will be securely stored at the Ochiai Hospital in a locked cabinet, accessible only to the trial team members. All the collected data will be entered into a password-protected Excel 2019 sheet (Microsoft Corporation, Redmond, Washington, USA). These data will remain for 5 years after the end of the trial, and will thereafter be shredded and disposed of with great care to protect the participants’ personal information.

### Monitoring

This trial will be monitored by a person assigned by the CI in accordance with the Standard Operating Procedures for Monitoring at Medical Institutions. Onsite monitoring shall be conducted by visiting the medical institution for direct trial implementation system confirmation and source document inspection. Among the 80 patients, 10 will be monitored. However, the sampling rate will be increased by 30% of the total number of patients if a problem arises in even one patient. Monitoring will include verifying the clinical trial progress and confirming whether all the required procedural documents are present at the research office through electronic communication. Additionally, the monitor will record the information, materials, and reports obtained throughout the trial and store them securely. Monitoring reports will be made available to the Okayama University Certified Review Board.

### Interventions

All the participants will receive instructions regarding the MREP and transdermal gel. They will be provided with educational information about the advantages of lower-limb exercises in KOA and the importance of adherence to the MREP. Analgesic medication use will be allowed, including nonsteroidal anti-inflammatory drugs as transdermal gels for the knee joint. All participants can continue their normal daily activities, such as walking and stretching. However, they will be asked to avoid new invasive knee joint treatments, including surgery and fluid injection.

### Muscle resistance exercise programme

The MREP will implement the same content for both the intervention groups, with one training session per week to be held in a group and two sessions per week at home. Twelve group sessions will be held at the community centre in each district where an instructor will be present to ensure training quality and provide guidance. The Maniwa Agri-garden-project NPO provides the MREP instructors with a group session. The exercise instructors will have a 2-h lesson provided by an experienced physiotherapist from the Okayama University Hospital and will receive certified coaching insurance from the CI. Each group session will last 90 min, including a 15-min break.

The group MREP session will comprise an evidence-based programme designed by a physiotherapist at the Okayama University Hospital. The MREP is a multi-component exercise programme with a beneficial effect on the physical functions of patients with KOA, consistent with the current standard of care and clinical practice guidelines [51–53]. It includes a dynamic warm-up with range of motion stretches (approximately 10 min), MRE (approximately 25 min), balance training [54] (approximately 10 min), cool-down with stretches (approximately 5 min), and a coordinated dual-task section [55] (approximately 25 min). The MRE was designed based on the OARSI guideline [56, 57], a structured land-based exercise programme focusing on the four major lower-limb muscle groups (quadriceps, calf muscle, hamstrings, and gluteal muscles), and abdominal and back muscles in patients with KOA. The MRE section consists of chair-based and standing exercises, including knee extension, knee lift exercises from sitting and standing positions, heel raise, squats, and chair standing exercises. Each movement will take 6–8 s, with the participants counting the seconds out loud. Each exercise will comprise two sets of 8–10 repetitions with gradually increasing muscle load [54] and number of repetitions based on the participant's perceived exertion. Weeks 1–4 will have no weight load, and 1.0 kg ankle weights will be used to increase the muscle load from week 5. The exercise instructor will supervise the participants by providing verbal feedback to ensure that the target muscle groups obtain sufficient tension.

The home training session will be scheduled on two non-consecutive days per week. It will comprise a 25-min MRE, identical to that of the group session. Each participant will receive a pamphlet regarding the home training content and a calendar form pictorially depicting the MRE. Participants will have to ‘circle’ the days on which they have performed the MRE at home to track whether they have performed the exercise. Furthermore, exercise quality will be evaluated by writing a numerical self-assessment from 1 to 3 on the calendar (1: performed less than half, 2: performed half, but not all, 3: completed all). The instructor will check the calendar contents during the group session every 4 weeks and provide guidance to those who need instruction.

### Transdermal oestrogen gel

During the intervention, l’ oestrogel 0.06%®　(gel containing 0.06% oestrogen; Fuji Pharma, Tokyo, Japan) (Standard Commodity Classification Number of Japan 872,473, approval number: 21800AMY10135, YJ code: 2473700M2026) [58] or placebo gel will be used. The transdermal oestrogen gel used in this trial is a clear, colourless gel containing 0.54 mg oestradiol per push (0.9 g), with an internal volume of 80 g per bottle [58]. The gel-type application prescribed by the CI will be applied once daily at a fixed time before beginning the MREP; one push should be applied as widely and thinly as possible on the anterior surface of the thigh with the palm. To ensure blinding, an unblinded pharmacist, who does not prescribe and treat subjects directly, will be set up to apply the bottle sticker. The bottles containing the oestrogen or placebo gel will be designed to ensure an accurate and uniform quantity dispensation with each push. The bottles will be packaged and distributed with a sticker bearing the participant identification codes. The bottles will be stored indoors at 1–30 °C to avoid heat, moisture, and sunlight. The placebo gels will be composed of ingredients similar to the base drug substance of the oestrogen gel, with comparable colouration, odour, and texture. The main ingredients of the base are ethanol, which is also used in the actual drug xanthan gum [59] as a viscosifying agent, and glycerol [60] as a moisturising ingredient. Both substances have already been proven to have no effect on the human body and are used in commercial moisturisers [59, 60]. The placebo drug will be prepared by an unblinded pharmacist at the Ochiai Hospital and injected into bottles, which will appear the same as the actual drug bottles, ensuring the quality of external blinding. The bottles will be checked during outpatient visits conducted one month after starting trial drug administration to check for side effects, and the amount used will be determined based on the amount remaining in each bottle.

### Outcome assessment

Outcome assessment will include baseline measurements of participants' anthropometric data and outcomes. At baseline, a physiotherapist will measure the height, weight, and upper arm, thigh, calf, abdominal, and gluteal circumferences and calculate the body mass index (BMI). The resting blood pressure and heart rate will be measured simultaneously. Outcome examinations will be performed at baseline before allocation, and 3 and 12 months after intervention initiation (Fig. 1). Outcomes will be measured by physical therapists with at least 5 years of clinical experience.

The primary outcome will be the 3-month and 12-month changes from the baseline physical performance according to the CS-30 score. The CS-30 devised by Jones is highly reproducible and has been shown to correlate with the quadriceps muscle strength and the ability to balance, walk, and perform ADL [61]. Since KOA-related knee pain reduces the ability to perform vertical movements, CS-30 is also reliable for functional assessment of inactivity due to KOA [62]. CS-30 uses an armless folding chair with a seat height of 40 cm. The participants will be seated in the middle of the chair with their back straight, feet shoulder-width apart, and arms crossed at the chest, and will be encouraged to complete as many full stands as possible within 30 s [61]. They will be instructed to sit fully between each stand. The measurer will silently count the correct stand completions after letting the participant practice once or twice.

The secondary outcomes include:Change in the knee pain score assessed using the VAS and 12-item Short form survey (SF-12).

VAS will be used to assess knee joint pain before and after the intervention. The pain intensity will be indicated by a 10 cm black line (the left end for ‘no pain’ and right end for ‘the greatest pain imaginable’) on the questionnaire, and the participant will be asked to draw a line to indicate the level of her current pain. Health-related quality of life as pain in daily life will be assessed using the SF-12, which was validated as a shorter alternative to the SF-36 [63].2)Change in physical function according to the gait speed and timed up and go test (TUGT)

The participants will be asked to walk along an 11 m straight line as quickly as possible, excluding the first and last 3 m. The 5-m walking time will be measured twice and the better result will be considered. The gait speed will be calculated as distance (m)/time (s). The TUGT measures the time taken to walk, after sitting in a chair, and turning around at a cone 3 m away to walk back and sit in the chair again. The TUGT is widely used in geriatric settings to assess lower-limb strength and fall risk [64].3)Change in muscle strength according to the hand-grip strength and knee extension strength (KES)

We will use a digital hand-grip dynamometer (Takei-kiki Corp., T.K.K5401) to measure the hand-grip strength and a hand-held dynamometer (HHD) with a fixing belt (Anima Corp., Mu-Tas F-2) to measure the KES. The participants will be instructed to maintain an upright posture, with the hip and knee joints bent at 90° in the end-sitting position. The HHD pad will be placed on the participant's shin, with the pad secured to the chair with a fixing belt. The operator will provide light support to prevent the pad from shifting during measurement [65]. The participant will gradually increase force to maximise knee extension for 5 s and hold the knee joint for 2 s at the point of maximum extension. Each strength measurement will be performed on the left and right sides and the higher value will be considered. The maximum force will be recorded in kilograms (kg) for the hand-grip strength and in kilogram-force (kgf) for the KES. The KES with HHD will be normalised to their mass (kgf/kg). An average KES of 18.8 ± 3.2 kgf in healthy women in their 80 s [66] and a positive correlation (r = 0.385) between KES and sit-ups [67] have been previously reported.4)Changes in muscle mass assessed by bioelectrical impedance analysis (BIA)

To assess muscle mass, body composition will be obtained by BIA measurements using the Tanita MC-780AN and Tanita Zaritz BM-220 (Tanita Corp., Tokyo, Japan) instruments. Appendicular skeletal mass (ASM, kg), BMI (kg/m^2^), skeletal muscle index (ASM/m^2^), total lean mass (TLM, kg), Body muscle index (TLM/weight × 100), and fat-% will be the body composition variables.5)Blood sampling

The levels of albumin, creatinine, bilirubin, alanine aminotransferase (ALT), aspartate aminotransferase (AST), gamma-glutamyltransferase, C-reactive protein, low-density lipoprotein, high-density lipoprotein, total cholesterol, triglyceride, oestradiol, insulin-like growth factor-1, calcium, 25-hydroxy vitamin D, d-dimer, fasting glucose, haemoglobin A1c, haemoglobin, and haematocrit and the white blood cell (WBC) and platelet counts will be assessed in all participants at baseline and after the intervention.6)Neuropsychological assessment

A verbal fluency test [68] will be performed for all participants at baseline and after the intervention.

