### Study design

The EPOK trial is a two-arm exploratory double-blinded RCT with a 12-week intervention period, and the outcomes will be measured at baseline, 3 months, and 12 months. Figure 1 outlines the RCT phases. Eighty participants will be identified and randomly categorised into two groups: (1) MREP with transdermal oestrogen gel and (2) MREP with placebo gel. Eligibility will be assessed during screening. The Okayama University Hospital and Ochiai Hospital will conduct this trial. We have organised the EPOK trial team, including the Maniwa City Community General Support Center, which will assist with recruitment via telephone, mail, local newspapers, and public health seminars. The non-profit organisation (NPO) of the agri-garden project will assist with MREP coaching. Figure 2 outlines the trial design schedule following the SPIRIT guidelines [38].

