### Sample size and power analysis

The sample size calculations were based on previously published data on increased lower extremity strength with MRE and ERT [47]. The rate of increase in the muscle strength during ERT is 5%–17% [34]. Positive correlations (*r* = 0.75) have been reported regarding the relevance of CS-30 scores on knee extension strength [47]. The average CS-30 score in patients with KOA is 9.2 repetitions [48]. Assuming that ERT can be expected to increase the CS-30 score by 13%, this sample size allows the detection of 1.2 times the primary outcome improvement (increased CS-30 score), in addition to an increase of 2.68 repetitions (1.90–3.47 repetitions, *p* < 0.001; I2 = 0.50%) due to the MREP alone [49]. The required sample size is 36 persons per group, calculated with an 80% one-sided test setting power, 5% alpha, and a 0.6 effect size (Cohen's d). The target size is set to 40 per group to account for a dropout rate of approximately 10%. Reports have shown that ERT has a low-to-moderate effect on lower extremity strength [34, 49, 50] and that ERT has improved knee pain and joint function in patients with KOA [29, 31]; therefore, we assume that ERT will have a slightly larger-than-moderate effect.

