### Statistical analysis

The MREP participants will be assigned to either the oestrogen or placebo group. Data will be aggregated for the assigned analysis participants at baseline, 3 months, and 12 months after the intervention. The target population will be the full analysis set, defined as all the randomised participants who have started their trial treatments.

The statistical analysis will be based on the intention-to-treat and per-protocol principles. The participants’ demographic background and baseline characteristics will be described as appropriate, with data presented as mean and standard deviation for continuous variables that appear to be approximately normally distributed, as medians and interquartile ranges for other continuous variables, and as counts and percentages for categorical variables. Linear regression analysis will be performed for a statistical comparison of the primary and secondary outcomes between the oestrogen and placebo groups. The relationship between the intervention and endpoints will be calculated as a regression coefficient with a 95% confidence interval. The covariate distribution is expected to be consistent across the groups due to randomisation. Therefore, only the presence or absence of intervention will be used as an explanatory variable for the linear regression analysis. However, the variable distribution will be biased by chance due to allocation; thus, the variable is added to the explanatory variables and an adjustment is made. We will adopt a complete case analysis as the primary analysis if the proportions of missing data are < 5%. Multiple imputations will be conducted if imputation of > 5% is required for the amount of missing data for an outcome, and the method will be reported.

The statistician, who is blinded to the allocation, will perform the analysis at the Department of Obstetrics and Gynaecology, Graduate School of Medicine, Dentistry, and Pharmaceutical Sciences, Okayama University. The validity of the analysis will be verified by the Centre for Innovative Clinical Medicine and Department of Epidemiology of the Okayama University as a third-party institution.

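### The primary outcome is the CS-30 change at two time points, but the sample size covers one test and no rule says whether success needs either or both

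*Protocol article*

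**What the plan says.** - **Primary outcome** (Outcome assessment): "The primary outcome will be the 3-month and 12-month changes from the baseline physical performance according to the CS-30 score". Two changes are named and neither is given priority.
- **Visit timing** (Outcome assessment): "Outcome examinations will be performed at baseline before allocation, and 3 and 12 months after intervention initiation".
- **Visit timing** (Statistical analysis): "Data will be aggregated for the assigned analysis participants at baseline, 3 months, and 12 months after the intervention". Read literally, this starts the clock at a different point.
- **Design** (Study design): "The EPOK trial is a two-arm exploratory double-blinded RCT with a 12-week intervention period".
- **Sample size** (Sample size and power analysis): 36 per group, "calculated with an 80% one-sided test setting power, 5% alpha, and a 0.6 effect size", raised to 40 per group for about 10% dropout. No time point is named.
- **Analysis** (Statistical analysis): linear regression on treatment group for all primary and secondary outcomes, reported with 95% confidence intervals. No time point is singled out, and no model or test joins the two visits.

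**The concern.** A primary outcome made of two comparisons needs a rule that turns two results into one conclusion. Without it, the stated alpha and power describe a single test that the protocol does not identify. If success at either visit counts, there are two chances of a false positive. If both visits must succeed, power is limited by the weaker of the two.

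The visits also measure different things. The 3-month value is taken at about the end of the 12-week intervention. The 12-month value is taken long after it and measures persistence. The sample size argument concerns a gain from oestrogen on top of the gain from the exercise programme, and says nothing about how much of it should remain after both stop. A benefit at 3 months with none at 12 is a plausible result, and the protocol gives the reader no way to classify it.

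**Working it through.** **Inputs from the protocol.** One-sided alpha 5%, power 80%, d = 0.6, 36 evaluable per group, about 10% dropout, a 12-week intervention, visits at 3 and 12 months, 95% confidence intervals.

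**Assumptions, not in the protocol.** The correlation r between the two test statistics, taken from 0 to 0.9. The 12-month effect if it wanes, illustrated by d = 0.5 and d = 0.3.

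**1. Reproduce the stated size.** For a two-sample t test at one-sided 5% and d = 0.6, the noncentral t distribution gives 79.96% power at 35 per group and 80.9% at 36. So 36 is exactly the size for one comparison at full alpha. With dropout, 36 / 0.90 = 40.

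**2. Two tests.** Use the bivariate normal with mean d × √(36/2) for each statistic:
- d = 0.6: 0.6 × 4.243 = 2.546
- d = 0.5: 2.121
- d = 0.3: 1.273

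The critical value is 1.645 at one-sided 5%, or 1.960 if benefit means a 95% interval lying above zero (one-sided 2.5%).

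- Either rule, no effect at either visit: error = 1 − P(Z1 < c, Z2 < c). At r = 0 and one-sided 5% this is 1 − 0.95² = 9.75%.
- Both rule, no effect at either visit: error = P(Z1 > 1.645, Z2 > 1.645).
- Both rule, power: the same joint probability with the means above.

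| r | Either: error, one-sided 5% | Either: error, 95% CI | Both: error | Both: power, d 0.6 then 0.6 | Both: power, d 0.6 then 0.5 | Both: power, d 0.6 then 0.3 |
|---|---|---|---|---|---|---|
| 0 | 9.75% | 4.9% | 0.25% | 67% | 56% | 29% |
| 0.3 | 9.3% | 4.8% | 0.7% | 69% | 59% | 32% |
| 0.5 | 8.8% | 4.5% | 1.2% | 71% | 61% | 33% |
| 0.7 | 8.0% | 4.2% | 2.0% | 73% | 64% | 35% |
| 0.9 | 6.8% | 3.5% | 3.2% | 77% | 67% | 35% |

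For comparison, the 12-month test alone has power Φ(2.121 − 1.645) = 68% at d = 0.5 and Φ(1.273 − 1.645) = 35% at d = 0.3.

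**3. Equal alpha split.** At one-sided 2.5% per visit and 36 per group, power per visit is 71% (noncentral t). Restoring 80% per visit needs 45 evaluable per group, and 45 / 0.90 = 50 randomised per group.

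**4. Time off treatment.** 12 weeks = 84 days, and 365 − 84 = 281 days, about 9.2 months. If the wording of the Statistical analysis section is taken literally, both visits move 12 weeks later, and even the 3-month value would be taken about 3 months after treatment ends.

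**The case against.** The strongest reply has four parts.

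- **Exploratory trial.** Strict familywise control is a confirmatory standard, and the Study design section calls the trial exploratory. This stands as a reason to lower the severity. It does not remove the point: the protocol still sets a primary outcome, an alpha and a power, and its Discussion looks ahead to proof that oestrogen is effective.
- **The analysis plan may settle it.** Testing order and alpha allocation are often left to a document not shown here, so the missing alpha split alone is no finding, and nobody can say that the choice will be made after seeing the data. What stands is internal to the protocol: the stated primary outcome has two parts, and the stated alpha and power fit one.
- **Inflation is not shown.** A reader might infer that the false-positive rate is simply above 5%. The protocol does not support that. It follows only from an either rule, which is never stated, combined with the one-sided 5% that appears only in the sample size section. With the 95% interval as criterion, the either rule gives 3.5% to 4.9%.
- **The 12-month test is not doomed.** A reader might also infer that any wash-out makes it fail, or that the off-treatment gap raises type I error. Neither is right. At d = 0.5 the test keeps 68% power, and the gap does not affect type I error. The protocol gives no basis for assuming a halved effect, so d = 0.3 is only an illustration.

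The difference in clock wording is probably loose drafting, since Outcome assessment is explicit. It is an editorial correction and adds nothing to the multiplicity argument.

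**Conclusion.** The point holds as a mismatch between the primary outcome and the sample size. Two time points are primary, the trial is sized for one test, and the success rule is not stated. At the one-sided 5% used for sizing, neither natural rule delivers the stated design. An either rule gives 6.8% to 9.75% familywise error. A both rule is conservative when there is no effect at either visit (0.25% to 3.2%), but reaches only 67% to 77% power if d = 0.6 persists, 56% to 67% if the 12-month effect is d = 0.5, and 29% to 35% if it is d = 0.3. All ranges rest on the assumed correlation of 0 to 0.9 and on 36 evaluable per group.

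The 9-month gap matters for interpretation only: it separates an end-of-treatment question from a persistence question, and so leaves a split result undefined. Severity: should be fixed, given the exploratory label.

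**What to change.** Before unblinding, name the CS-30 change from baseline to 3 months after intervention initiation as the single primary endpoint. Test the 12-month change second, and only if the 3-month test succeeds. This fixed sequence keeps alpha at 5%, and 36 evaluable (40 randomised) per group stands for the 3-month test. No visit changes. The cost is an amendment to the wording of the protocol, any analysis plan and the registry entry, and the 12-month result can no longer support a positive claim on its own.

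If both time points are to stay primary, state the rule and restate the power: about 71% per time point at 36 per group under an equal alpha split, or 67% to 77% jointly if both are required and d = 0.6 persists. Under the split, 80% per time point would need 45 evaluable, or 50 randomised, per group.

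In either case, state the significance threshold that decides success, and bring the visit timing in Statistical analysis into line with Outcome assessment.

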### Adverse events

The drug safety tests in this trial include liver and renal function tests, serum cholesterol levels, mammography, and gynaecological examination. Collection and examination of these parameters and all blood samples will be conducted at the Ochiai Hospital, Okayama, Japan. Participants will have 24-h access to call and visit the emergency department of Ochiai Hospital if any adverse event is suspected. A standardised protocol for potential adverse events will be available at the Ochiai Hospital with the CI’s contact number and a manual for examination and testing. All the adverse events will be recorded and monitored until the end of the trial. All significant and severe adverse events will be recorded in the clinical notes and written in a case report form, which includes the adverse event details, such as the timing of onset and resolution, extent, treatment, outcome, and severity assessment. Significant and severe events will be reported by the Okayama University Clinical Research Board (CRB) using the application form on the internet site. If participants have significant or severe adverse events, the CRB or CI will determine whether the participants can continue with or withdraw from the trial and inform them accordingly. These participants will be referred and treated for each event depending on the symptoms and severity, even if they are withdrawn from the trial.

The participants may report minor adverse events [58, 69] including:Reproductive organ: irregular vaginal bleeding, increased vaginal discharge, vulval irritation or itching, increased leiomyoma size, endometriosis recurrenceBreast: tender breastsSkin at site of gel application: redness, irritation, itching, pigmentation, hivesNervous system: headache, migraine, weakness, dizziness, depression, nervousness, rapid changes in mood, difficulty sleepingCardiovascular: palpitation, rise in blood pressureGastrointestinal: abdominal distension, nausea, abdominal cramps, vomiting, heartburnLiver function: increased liver enzymes (AST, ALT, alkaline phosphatase)Blood: decreased WBCs, anaemiaMusculoskeletal: back pain, lower limb, ankle, or finger swelling, arthritisOthers: Increased triglycerides, fatigue, tinnitus, nasal bleeding, weight gain

Significant adverse events [59, 70] include heavy vaginal bleeding, jaundice, heavy abdominal distension, and oliguria.

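### Knee extension strength is divided by a body mass whose visit is not stated; same-visit mass may be altered by treatment and could understate a 3-month strength gain

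*Protocol article*

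**What the plan says.** All of these statements are in the protocol article.

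- **Strength (Outcome assessment, item 3).** "The maximum force will be recorded in kilograms (kg) for the hand-grip strength and in kilogram-force (kgf) for the KES". The next sentence makes the analysed quantity a ratio: "The KES with HHD will be normalised to their mass (kgf/kg". No visit is named for the mass.
- **Muscle mass (Outcome assessment, item 4).** Bioelectrical impedance (BIA) is the only method given: "To assess muscle mass, body composition will be obtained by BIA measurements". The variables include appendicular skeletal mass (ASM), the skeletal muscle index (SMI) and total lean mass (TLM), and the list ends with "Body muscle index (TLM/weight × 100), and fat-% will be the body composition variables".
- **Weighing.** The opening of Outcome assessment states weighing explicitly only at baseline. BMI and TLM/weight are listed as change outcomes, however, so weight must also be taken at follow-up.
- **Possible side effects (Adverse events).** The minor events that participants may report include "back pain, lower limb, ankle, or finger swelling" and, under other events, "Increased triglycerides, fatigue, tinnitus, nasal bleeding, weight gain". No frequency, size or comparison with placebo is given.
- **Timing (Study design).** The intervention lasts 12 weeks; outcomes are measured at baseline, 3 months and 12 months.

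**The concern.** A ratio outcome is a clean measure of its numerator only if treatment leaves the denominator alone. If oestrogen raises body mass, through fluid or otherwise, KES per current kilogram falls relative to placebo even when strength is identical. Randomisation and blinding do not remove this, because the change in mass arises after randomisation.

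Impedance methods infer lean tissue from electrical conduction, which depends on body water. That is general measurement knowledge and not a statement in the article. Limb fluid can therefore be counted as lean mass, which would push ASM, SMI and TLM upward while KES/kg is pushed downward.

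The Aim section hypothesises a gain in lower-extremity strength, and the Discussion relies on the secondary outcomes, without biopsy, to describe the effect of oestrogen on the musculoskeletal system. What is at risk is the reading of these secondary results at 3 months: a real strength gain could be understated, and a fluid change could be described as muscle.

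**Working it through.** **Figures from the article.** Strength gain on oestrogen, 5–17% (Sample size and power analysis). Reference KES, 18.8 ± 3.2 kgf (Outcome assessment). The article gives no body mass, weight change, ASM or TLM.

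**Assumptions.** Baseline mass W = 50 or 55 kg. Mean between-arm difference in weight change D = 0 to 1.5 kg. Zero belongs in the range because no rates are given.

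**Step 1. KES/kg with strength unchanged.** Relative fall = 1 − W/(W + D) = D/(W + D).

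**Step 2. What remains of a true gain g.** Apparent gain = (1 + g)/(1 + D/W) − 1.

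| D (kg) | W (kg) | Fall, strength unchanged | True 5% appears as | True 17% appears as |
|---|---|---|---|---|
| 0 | either | 0% | 5.0% | 17.0% |
| 0.5 | 50 | 1.0% | 4.0% | 15.8% |
| 0.5 | 55 | 0.9% | 4.1% | 16.0% |
| 1.0 | 50 | 2.0% | 2.9% | 14.7% |
| 1.0 | 55 | 1.8% | 3.1% | 14.9% |
| 1.5 | 50 | 2.9% | 1.9% | 13.6% |
| 1.5 | 55 | 2.7% | 2.2% | 13.9% |

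The largest loss shown (D = 1.5, W = 50) is (5 − 1.94)/5 = 61% of a 5% gain, but (17 − 13.59)/17 = 20% of a 17% gain.

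**Step 3. The same shift in SD units.** 18.8 × 0.029/3.2 = 0.17 SD at the top of the range and 0 at the bottom. A true 5% gain is 18.8 × 0.05/3.2 = 0.29 SD; a true 17% gain is 1.0 SD.

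**Step 4. If few women are affected.** If 10% of the oestrogen arm gained 1 kg and nobody else did, D = 0.1 kg and the fall is 0.1/50.1 = 0.2%.

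**Step 5. Impedance variables.** Assume TLM 36 kg and W 50 kg, with 1 kg of retained fluid of which a share φ is read as lean.

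- TLM rises by φ × 1/36: 1.4% at φ = 0.5 and 2.8% at φ = 1, with no muscle gained.
- TLM/weight × 100 starts at 72.0. It becomes 36.5/51 = 71.6 at φ = 0.5 and 37/51 = 72.5 at φ = 1, so its direction is not determined.
- For ASM, assumed 14–16 kg, 0.5 kg of limb fluid read wholly as lean adds 0.5/16 to 0.5/14, or 3.1–3.6%.

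**Step 6. With the denominator fixed.** Absolute kgf, or kgf over baseline mass, returns g unchanged for every D.

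**Step 7. What is untouched.** The sample size rests on the chair stand test (CS-30). With d = 0.6, one-sided 5% alpha and 80% power, a t-test needs 35.04, rounded up to 36 per group; 36/0.9 = 40. This reproduces the stated figures, and nothing above enters the calculation.

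**The case against.** The strongest reply is that no bias has been shown. Swelling and weight gain stand in a long list of events that participants may report, alongside tinnitus and nosebleeds. A reader might infer that oestrogen will raise body mass, that the distortion falls in one arm only, and that the trial is set to report muscle without strength. The article does not support this: it gives no rate, size or arm comparison. That part of the objection stands in full.

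It can also be said that same-visit mass is only a reading. If baseline mass is meant, the KES problem disappears, and the full protocol may say so. This stands as far as it goes, but the ratio is fixed in the article while its denominator is not, and the change outcomes that need follow-up weight make same-visit mass the natural reading.

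Strength per current kilogram is also a legitimate quantity, since a heavier woman has more to lift. That is fair, and is why it should be kept as descriptive. It answers a different question from the hypothesised gain in lower-extremity strength.

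Finally, unaffected measures exist: absolute kgf, grip strength, gait speed, the timed up and go test and CS-30. This limits the harm. Recording absolute kgf does not settle the matter, however, while the text names the normalised value.

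One tempting remedy fails: accepting an ASM gain only when body water has not risen. Impedance derives lean mass and water from the same signal, so a genuine muscle gain would fail that test too.

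**Conclusion.** The point holds as a cheap improvement to secondary outcomes, not as a demonstrated bias. The KES denominator is not fixed, and on its natural reading treatment may alter it. Under the assumed 0 to 1.5 kg mean arm difference at 50–55 kg, KES/kg is lowered by 0 to 2.9%. That matters if the true gain is near 5% and much less if it is near 17%. The true size cannot be obtained from the article and may be close to zero.

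For impedance, upward distortion is possible in ASM, SMI and TLM but has no clear direction for TLM/weight. Both issues concern mainly the 3-month visit, because by 12 months treatment has been over for about nine months. CS-30 and the sample size stand.

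**What to change.** 1. Make absolute kgf the main KES variable, or kgf divided by baseline body mass at every visit. Adjust the comparison for baseline KES. Keep kgf per current kilogram as descriptive.
2. Report 3-month ASM, SMI and TLM beside weight change and recorded swelling, by arm. State that impedance alone cannot separate muscle from fluid. Do not add a body-water condition for accepting an ASM gain.

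The cost is wording, plus one covariate in the regression for this outcome. Absolute kgf and baseline weight are already collected, follow-up weight is implied by the listed change variables, and all adverse events are to be recorded. The downside is that strength relative to current body mass becomes descriptive and any muscle-mass claim has to be more cautious.
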